#### Secondary outcomes

The following secondary effect measures will be collected at baseline, immediately after the intervention (for the control group 5 weeks after baseline) as well at the 6-, 12- and 24-month follow-ups.

##### *Severity of suicidal ideation*

Severity of suicidal ideation will be rated with the Columbia-Suicide Severity Rating Scale (C-SSRS) [35]. Scores range from 0 to 5, where higher scores indicate more severe ideation.

##### *Depressive symptoms*

To assess depressive symptoms the Montgomery-Åsberg Depression Rating Scale (MADRS) [42], will be applied. Each item yields a score of 0 to 6; the overall score thus ranges from 0 to 60. Higher MADRS score indicates more severe depression.

##### *Anxiety symptoms*

Generalized Anxiety Disorder 7-item scale (GAD-7) [43] will be used to assess anxiety symptoms. Each item yields a score of 0 to 3; the overall score thus ranges from 0 to 21. Higher GAD-7 score indicates more severely elevated anxiety.

##### *Coping style*

Coping styles will be assessed by Brief - Coping Orientation to Problems Experienced Inventory (Brief-COPE) [44]. The 28-item self-report scale is scored from 1 to 4 where 1 = I haven’t been doing this at all 2 = A little bit 3 = A medium amount 4 = I’ve been doing this a lot. The Brief COPE consists of 14 subscales, each representing a specific coping strategy. Each subscale consists of 2 items, making the full scale 28 items in total. Scores are presented as average scores (sum of item scores divided by number of items), indicating the degree to which the respondent has been engaging in that coping style.

##### *Quality of life*

Health-related quality of life is rated with the The EuroQol 5-Dimension 5-Level (EQ-5D-5 L) [45]. The EQ-5D-5 L consists of the EQ-5D descriptive system and the EQ visual analogue scale (EQ VAS). The descriptive system comprises five dimensions (mobility, self-care, usual activities, pain/discomfort and anxiety/depression): Each dimension has 5 levels: A higher 1-digit number mean a worse outcome. Higher scores on the EQ VAS mean a better outcome.

##### *Psychosocial conditions*

In addition, participants will fill in a brief psychosocial questionnaire with 6 single item questions inspired by scales employed in previous studies focusing on older adults’ mental health [46, 47, 48, 12]. Items are scored on a four-point Likert-scale (0–3). “Do you feel that you matter to others?” “Have you felt like a burden to others recently?” “Do you believe others would be better off without you?” “Have you had problems with loneliness recently?” “Do you feel that your situation has been hopeless recently?” “Have you had difficulties in your relationship with a partner, family member, or another important person recently?”

### Therapeutic alliance, health-care utilization, negative effects of treatment and feasibility measures

#### Therapeutic alliance

The Working Alliance Inventory-Short Revised (WAI-SR) [49], is used to measures therapeutic alliance on 12 items on a 7-point Likert scale from 1 = “never” to 7 = “always”, after the second ASSIP-OA session.

#### Health-care utilisation

We will assess psychiatric inpatient hospitalizations, as well as the number and type of psychiatric healthcare contacts, based on medical records at 12- and 24-month follow-ups.

#### Negative effects

Further, the Negative Effects Questionnaire (NEQ) [50], will be applied after the last ASSIP-OA session to answer the research question on side effects. NEQ contains of 32 items that are scored on a five-point Likert-scale (0–4) and differentiates between negative effects that are attributed to treatment and those possibly caused by other circumstances. At the end of the questionnaire there is also one open-ended question: “Describe in your own words if any other negative events or effects occurred, and what characterised them.”

#### Feasibility measures

The following feasibility measures is used to investigate if the modified ASSIP intervention is feasible in older adults: Acceptability will be addressed in the qualitative interviews with participants post intervention. Appropriateness is measured by Cronbach alpha and mean inter-item correlation in our questionnaires (see above under effect measures). Deliverability is measured by examining that all components of the ASSIP- OA are provided on the 3–5 sessions without having to stress through them. Video recordings will be used to explore this. Fidelity: To ensure good administration of the ASSIP-OA: (1) training manuals with checklists for the therapists will be used to check after each session, and (2) video recordings of randomly selected ASSIP- OA sessions (15%) are reviewed by independent assessors using a checklist to rate the therapist’s competence and adherence to the intervention (Adherence and Competence Scale (ACS)– [name] et al., soon to be submitted).

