## Objectives and hypothesis

This paper outlines the study protocol for our upcoming study, which aims to evaluate a modified version of the Attempted Suicide Short Intervention Program (ASSIP), specifically for older adults (65+), the ASSIP for older adults (ASSIP-OA), as an add-on to usual treatment. The efficacy of the ASSIP-OA intervention will be evaluated by comparing it to a control group receiving only treatment as usual (TAU).

The main hypothesis is that participants randomised to the add-on treatment condition - the ASSIP-OA intervention - will experience a preventive effect on suicide and suicide attempts within 6, 12, and 24 months following the index episode. Also, we anticipate participants in the experimental condition to show better improvement in psychiatric symptoms/severity of suicidal ideation/coping skills/quality of life (secondary outcomes). Additionally, we aim to investigate if the brief preventive intervention (ASSIP-OA) is feasible, based on its acceptability, appropriateness, deliverability and fidelity, and whether participants have fewer days of inpatient care or experience any negative side effects. Further, the study also includes a qualitative approach to explore what kind of challenges and opportunities (a) older adults and (b) ASSIP-OA therapists experience in relation to implementing the brief preventive intervention, and if the modifications that we made in ASSIP-OA are relevant for older adults.

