## Methods

### Study setting and design

This study is designed as a multicentre two-group parallel randomised controlled trial (RCT), to be conducted within psychiatric services in the Swedish regions of Västra Götaland, Skåne, and Halland. Several additional regions have shown interest and may be added. Participants are randomly assigned to either:

a brief 3–5 session preventive intervention (approx. 1 session per week), the Attempted Suicide Short Intervention Program for Older Adults (ASSIP-OA), which is an add-on to usual treatment.a control group receiving treatment as usual (TAU) only.

Measurements will be taken prior to randomisation and after the last session (or after 5 weeks for the control group) and follow-up measurements (see below) will be assessed at 6, 12 and 24 months after the last session. An overview of data to be collected at the various timepoints is shown in Fig. 1. Following the baseline measurement, randomisation will take place electronically via REDCap (Research Electronic Data Capture) [28] and will be conducted using block randomisation with varying block sizes and with an allocation ratio of 1:1 between intervention groups. The randomisation procedure was designed by a statistician at the University of Gothenburg, independent of the research group. Randomisation will be blinded to the data processors, as well as to the researchers and clinicians conducting the initial assessments and screening (prior to randomisation). The size of the randomisation blocks will remain undisclosed. Due to the design of the intervention, blinding participants to their assigned group will not be possible. As it is anticipated that usual treatment will vary somewhat between the study locations, it will be mapped for each patient. Data on clinical diagnoses, healthcare contacts and treatments for mental health concerns during 24 months before and after baseline measurements are derived from medical records.

The study will follow the CONSORT guidelines and was pre-registered at Clinical Trial.gov NCT06831942 on February 21, 2025 and revised May 21, 2025. The present study protocol follows the recommendations for clinical trial protocols from the SPIRIT Declaration [29, 30], see Supplementary material 1 for checklist.

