#### Exclusion criteria

Clinical diagnosis of dementia or Montreal Cognitive Assessment (MoCa) score less than − 2 standard deviations from the normative score for education and age [31]. Ongoing delirium, or any other condition impeding the comprehension of the study’s procedures and implications that hinder the provision of informed consent.Severe ongoing psychosis, severe ongoing substance use disorder, emotionally instable personality syndrome and any other condition that would require longer specialized treatment to reduce future suicidal behaviour (e.g. DBT).Terminal illness.Insufficient knowledge of the Swedish language (requires interpreter).Aphasia or other severe communication issue or severe hearing and/or severe visual impairment despite corrective aids that render the intervention unfeasible.

In connection with post-treatment data collection, a purposive sample of approximately 15 participants who took part in ASSIP-OA sessions will be asked to participate in an interview to generate a deeper picture of participants’ experiences of ASSIP-OA. In addition, we will use focus group interviews to examine ASSIP-OA therapists’ experiences of the training and application of ASSIP-OA in their clinical settings, including their experiences of obstacles and opportunities in connection with the delivery of ASSIP-OA. We anticipate that all the ASSIP-OA therapists (n = approx. 14) will be interested in taking part in two sets of focus groups, but participation is voluntary.

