Clinical psychologists and a psychiatrist, experienced in geriatric psychiatry in Sweden, have drawn on insights from the geriatric psychiatry clinic in Bern (personal communication, [name], 2025) to tailor the treatment protocol to the Swedish context. [name] stresses that it is not the specific components of ASSIP that require change, but rather that there should be a greater focus on the patient’s individual needs of support in areas such as loneliness, chronic pain, physical limitations and in some cases milder cognitive impairment. [name] highlights the need for a higher degree of flexibility when delivering ASSIP to older adults, especially for the “older older”. Providing home visits is one way to improve adherence [32]. Older adults may require extra support in communicating their needs. As most suicidal older adults are dealing with chronic medical conditions and have regular appointments with primary care, it is important to share the case conceptualisation with the patient’s GP and other relevant care providers, once permission is given by the patient. Moving to long term care was a particularly vulnerable time for older adults at the Bern clinic, an observation we have also made in our own Swedish research [33]. In such cases, ASSIP could better fit the older person’s needs by including a session with a nurse or other staff member at the care facility, chosen by the older adult, after the tree core sessions to support the translation of ASSIP warning signs and coping strategies into everyday life. Another reflection from the Bern clinical experience was that, while the video playback was not an issue for most older participants, some older men found it problematic to watch. This could be ameliorated by the therapist taking a more supportive role than they might have done with a younger patient. A more active role by the therapist may also be appropriate for older adults experiencing cognitive impairment. Enhancing problem-solving abilities is a key component of treatment protocols for individuals with suicidal tendencies and executive dysfunction [34].

**Table 1 Tab1:** Treatment protocol for the attempted suicide short intervention program for older adults (ASSIP-OA)

Session no	Session Components and Modifications

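### Acceptability rests only on about 15 interviews with people who attended ASSIP-OA sessions, so non-starters cannot be heard, early stoppers may not be, and no uptake or completion measure is assigned to it

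*Protocol article*

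**What the plan says.** The Objectives and hypothesis section sets out to learn whether ASSIP-OA is "feasible, based on its acceptability, appropriateness, deliverability and fidelity". The Feasibility measures section then assigns a measure to each component. For acceptability the whole entry is: "Acceptability will be addressed in the qualitative interviews with participants post intervention".

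The last paragraph under Exclusion criteria says who is interviewed and when: "In connection with post-treatment data collection, a purposive sample of approximately 15 participants", namely those "who took part in ASSIP-OA sessions will be asked to participate in an interview to generate a deeper picture of participants’ experiences of ASSIP-OA". In the intervention arm, post-treatment is tied to the final session (Study setting and design): "Measurements will be taken prior to randomisation and after the last session (or after 5 weeks for the control group".

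The same paragraph under Exclusion criteria plans focus groups with about 14 therapists, "including their experiences of obstacles and opportunities in connection with the delivery of ASSIP-OA". They are not assigned to acceptability.

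**The concern.** Whether people accept a programme shows first in whether they start it and stay with it. A frame built on attendance leaves out those who said no at the outset, and an approach made at post-treatment is less likely to reach those who left early. Both groups bear directly on acceptability.

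Feasibility is a stated aim, and the Discussion makes wider use of the results conditional on the programme proving feasible as well as effective. Under the plan as written, interviews could yield a favourable account of acceptability even if a sizeable part of the arm had declined the sessions.

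**Working it through.** **Size of the arm.** The Sample size section gives 60 per group, raised to 66 for 10% dropout. With 30% against 10%, two-sided 5% and power 0.80, the unpooled formula gives (0.30 × 0.70 + 0.10 × 0.90) × (1.960 + 0.842)² / 0.20² = 59; the pooled form gives 62. The stated 60 lies between them. 60 × 1.10 = 66, while 60 / 0.90 rounds up to 67. None of this affects the present point; 66 serves only as the size of the ASSIP-OA arm.

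**Who can be interviewed.** Reading the passages together, by attendance:

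| Randomised to ASSIP-OA and … | Can be interviewed under the stated frame? |
|---|---|
| attended no session | No. The person took part in no session, and has no last session to anchor the post-treatment contact. |
| stopped after one or two sessions | Possible, not ensured. No minimum attendance is required, but the invitation comes around post-treatment and no place is set aside. |
| completed the three core sessions | Yes. |

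**Whether another measure fills the gap.**

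- Appropriateness is measured by the internal consistency of the questionnaires.
- Deliverability and fidelity use recordings and checklists of sessions that took place.
- The WAI-SR is given after the second session and the NEQ after the last, so both depend on attendance.
- The focus groups give therapists' views.

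No feasibility component is assigned the number who start, the number who complete the core sessions, or the reasons for stopping.

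**Size.** About 15 / 66 = 23% of the arm is interviewed. That describes the frame and does not measure bias, since a purposive qualitative sample is not a survey.

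The document gives no uptake or acceptability rate, so any figure for overstatement is an assumption. Let *s* be the share of the arm not represented, *a* the proportion finding the programme acceptable among those represented, and *b* the proportion among the rest. The arm-wide value is (1 − s)a + sb, and the overstatement is a − [(1 − s)a + sb] = s(a − b). Assuming a = 90% and b between 20% and 50%:

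| s (assumed) | Overstatement, percentage points |
|---|---|
| 5% | 2 to 3.5 |
| 10% | 4 to 7 |
| 20% | 8 to 14 |
| 30% | 12 to 21 |

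If a = b the overstatement is 0, whatever s is. The table shows only how the effect depends on the two unknowns; it is not an estimate for this trial.

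**The case against.** The case for leaving the plan alone has several parts.

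- **Early stoppers.** A reader might infer that people who stop early are left out. The text does not say so: attendance at sessions is the only condition, purposive sampling is a usual way to seek out such cases, and the last session can be read as the last one attended. Under intention to treat, stopping therapy does not end data collection. This stands; the point is only that their inclusion is not ensured.
- **Dropout.** A reader might apply the 10% dropout to the arm and conclude that six or seven people will stop ASSIP-OA. That figure is expected loss from the trial, applied to both arms. It is not a rate of stopping therapy, so no such count follows.
- **Video playback.** The Treatment group section reports from clinical experience elsewhere that "some older men found it problematic to watch". A reader might take this as a predicted reason for leaving. The same passage says most older participants had no difficulty and that a more supportive therapist could help. It says nothing about stopping.
- **Qualitative question.** No acceptability proportion or threshold is planned, and interviewees can report what they disliked. This stands, and it is why the size cannot be computed. It does not bring in the people who never attended.
- **Evidence elsewhere.** Reporting to CONSORT should show how many received the allocated treatment, and therapists may speak about patients who left. Both help a careful reader, but the plan uses neither to judge acceptability.
- **Condensed article.** Detailed selection criteria commonly sit in the full protocol or interview guide, and their absence is no finding. The article does, however, state the measure, the frame and the timing, and that stated frame excludes non-starters.

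**Conclusion.** The point holds in a limited form. Acceptability has one measure, and its stated frame excludes everyone randomised to ASSIP-OA who attends nothing. Early stoppers may or may not be included. No uptake or completion measure is assigned to acceptability to offset this.

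Overstatement is the likely direction, on the assumption that people who decline or leave view the programme less favourably than those who attend. A reader might go further and say that acceptability will certainly look better than it is. The document does not support that: people may stay away for reasons unrelated to the programme, such as illness, and if their views match those of attenders there is no bias. The size cannot be derived from the document.

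The weakness concerns one component of a feasibility aim. The primary outcome, its analysis and the sample size are untouched. It is still worth correcting, because reasons for declining or stopping are hard to recover if they are not recorded at the time.

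**What to change.** **Feasibility measures.** Add as an acceptability measure the proportion of all participants randomised to ASSIP-OA who attend session 1, and the proportion who complete the three core sessions, each with a confidence interval. Record reasons for declining or stopping, including declining the video playback. With 66 in the arm, the 95% interval is at widest about ±1.96 × √(0.5 × 0.5 / 66) = ±12 percentage points, which is enough to tell high uptake from poor uptake.

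**Interview paragraph under Exclusion criteria.** Widen the frame to everyone randomised to ASSIP-OA. Reserve a few of the 15 places for non-starters and early stoppers, and invite them when they decline or stop instead of waiting for post-treatment.

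**Cost.** The number of interviews is unchanged. Attendance should be obtainable from the written appointments (Retention) and the therapists' per-session checklists (Feasibility measures), although the article does not say that it will be compiled; recording reasons adds a short entry. The downsides are that fewer completers are interviewed and that some people who declined or stopped will also decline an interview, so reserved places may go unfilled. The uptake and completion proportions would still cover the whole arm.

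### The only measure named for the appropriateness of ASSIP-OA is the internal consistency of the outcome questionnaires, which does not assess the intervention

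*Protocol article*

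**What the plan says.** Objectives and hypothesis (Protocol article) sets an additional aim: to find out whether ASSIP-OA is "feasible, based on its acceptability, appropriateness, deliverability and fidelity". All four components are properties of the intervention. Feasibility measures confirms this, since the measures listed there are "used to investigate if the modified ASSIP intervention is feasible in older adults".

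That section then gives each component its measure:

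- **Acceptability:** "Acceptability will be addressed in the qualitative interviews with participants post intervention".
- **Appropriateness:** "Appropriateness is measured by Cronbach alpha and mean inter-item correlation in our questionnaires", with a pointer back to the effect measures. No other measure is named.
- **Deliverability:** video review of whether all session components are delivered without rushing.
- **Fidelity:** therapist checklists after each session, and independent rating of 15% of recorded sessions for adherence and competence.

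On timing, Study setting and design places the first assessment before allocation and has the control group assessed as well. Secondary outcomes repeats the schedule: baseline, after the intervention (five weeks after baseline for controls), then 6, 12 and 24 months.

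The interviews draw on "a purposive sample of approximately 15 participants who took part in ASSIP-OA sessions" (last paragraph under Exclusion criteria). The same paragraph plans two sets of focus groups with about 14 therapists. Objectives and hypothesis also has a qualitative aim on whether the adaptations matter to this age group. None of this is linked to appropriateness.

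**The concern.** Three of the four components have a measure directed at the intervention: what participants say about it, what happens in the sessions, and how well therapists keep to it. Appropriateness alone is measured on the outcome instruments. Cronbach's alpha and the mean inter-item correlation describe how the items of a scale vary together. They carry no information on whether a programme fits the people it is offered to.

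This is a stated measure that does not match its target, not a detail left to a fuller document. Adapting ASSIP to older adults is what is new about the programme, and the Discussion makes later implementation depend in part on its proving feasible. If the text is followed literally, a set of alpha values would be reported as evidence on the appropriateness of ASSIP-OA, and that inference would not be valid.

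**Working it through.** The protocol states no alpha threshold or target, so there is no figure to reproduce. The check sets the sections side by side and adds a short illustration.

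**1. Object of measurement.** Objectives and hypothesis and the opening of Feasibility measures both name the intervention as the object. The appropriateness sentence names the questionnaires. The two do not match.

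**2. When and in whom the statistic exists.** The effect measures are completed before randomisation and by both arms. Alpha can therefore be computed at baseline, when nobody has received ASSIP-OA, and in the control arm, where nobody will. A quantity fully available without the intervention cannot measure the intervention's fit.

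**3. Response to a treatment effect.** For k items,

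alpha = k/(k-1) × (1 - sum of item variances / variance of the total score).

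Adding a constant to every item changes no variance and no covariance, so alpha and the inter-item correlations stay the same. To illustrate, assume a ten-item one-factor scale with item = 0.6 × factor + 0.8 × error. Each item then has variance 0.36 + 0.64 = 1 and the inter-item correlation is 0.36. The expected alpha is 10 × 0.36 / (1 + 9 × 0.36) = 3.6/4.24 = 0.849. Simulated with 66 participants (the planned arm size) and 2,000 runs:

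| Shift on every item | Mean alpha | Mean inter-item correlation |
|---|---|---|
| -1 | 0.845 | 0.359 |
| 0 | 0.844 | 0.358 |
| +1 | 0.845 | 0.359 |

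The differences are simulation noise. The scale and loading are assumptions, and only a uniform shift was tried. A treatment that changed the spread of scores could move alpha, but that would still describe the scores and not the suitability of the programme.

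**4. Fit of alpha to the listed instruments.** Alpha is undefined for one item, because k - 1 = 0. That applies to the EQ VAS, to the C-SSRS ideation severity score (0 to 5), and to each of the six psychosocial questions, which are described as single items. Each Brief-COPE subscale has two items. With two standardised items, alpha = 2r/(1 + r), which is 0.33, 0.57 and 0.75 at assumed correlations of 0.2, 0.4 and 0.6. Even as a psychometric summary, alpha suits only the longer scales.

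**The case against.** The strongest reply is that appropriateness will be studied anyway. The qualitative aim asks about the relevance of the adaptations, participants will be interviewed, and therapists will discuss in focus groups what helped and hindered delivery. That stands, and it limits the point. A reader might infer that one of the four feasibility questions cannot be answered at all. The protocol does not support that reading: relevant data are planned, but they are not assigned to this component.

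The authors may instead have meant that the questionnaires are appropriate for older respondents. That would be a reasonable thing to check, but neither section says so, and the intervention's appropriateness would then have no named measure.

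Two further inferences are tempting and should not be drawn:

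- **That early stoppers have no voice.** The interview sample is defined by having taken part in sessions, not by finishing them. Someone who stopped after the first session qualifies. Only people who attended no session fall outside the wording. The Negative Effects Questionnaire, with its open question, is another route for poor experiences.
- **That alpha tilts the verdict towards feasibility.** No threshold or direction is stated, and alpha could well be low on the two-item subscales. A statistic unrelated to fit is uninformative about it and favours neither answer.

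It is also fair to say that feasibility is an additional aim, and that nothing in the efficacy analysis depends on this sentence.

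**Conclusion.** The point holds in a limited form. The only measure the protocol names for the appropriateness of ASSIP-OA describes the outcome scales and cannot show whether the intervention suits older adults. This affects one of four components of an additional aim. The other three have measures directed at the intervention, and the primary and secondary efficacy outcomes are unaffected.

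The conclusion rests on the protocol's own wording about what is measured, when and in whom. It does not depend on the simulation, which only illustrates it under assumed loadings. The point is worth correcting because the text fixes an invalid inference and the data for a better one are mostly planned already.

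**What to change.** In Feasibility measures, replace the appropriateness sentence so that:

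1. Appropriateness is assessed from the planned participant interviews and therapist focus groups, using their questions on whether the adaptations suit this age group. State which topics serve acceptability and which serve appropriateness.
2. These are supported by descriptive counts among everyone randomised to ASSIP-OA: how many start, how many complete the three core sessions, and how many use the optional sessions and home visits. Label these as uptake. A poorly fitting programme can be completed, and a fitting one can be stopped because of illness, so completion is not appropriateness itself. With 66 allocated and an assumed 80% completing, the 95% half-width is 1.96 × √(0.8 × 0.2/66) = 0.097, about 10 percentage points. That is the precision of the uptake figure, not a measure of the defect.
3. Alpha and mean inter-item correlation are reported separately, as a check of the multi-item scales in this population.
4. The purposive sample of about 15 deliberately includes some participants who stopped early, which the present wording allows.

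The cost is slightly more descriptive reporting and possibly harder recruitment of early stoppers. Therapist checklists after each session are already planned. The article does not say whether they record the place of the session, so a field may be needed. Interviewing people who never started would be a larger step, because it changes the sampling frame. Under Trial status, an important modification requires an ethics application and an update of the registration. The correction proposed here does not depend on that step.
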